### Data management

The handling of personal data will comply with the Personal Data Protection Act in The Netherlands. Data will be recorded using the two ways of data collection described below.Data from the face-to-face contacts will be recorded on data collection forms and centrally collected at Medisch Spectrum Twente. The study data manager will record all the collected data in a Microsoft Access 2007 database.The majority of data will be recorded by Tactus Addiction Treatment – a regional addiction care organization with experience in web-based treatment - using online questionnaires which will be offered to both treatment groups. Individual patients and counsellors will have a login with username and password secured by Secure Sockets Layer to the application. All data transferred between the patient’s personal computer and the application will be encrypted and sent via the https protocol. All data will be encrypted and stored on servers in secure data centres within the Netherlands. Daily backups of the server will be made to ensure further data security.

### Data analysis/Statistical methods

Baseline characteristics will be displayed as means with standard deviations (SD) or medians with interquartile range (IQR) for continuous variables depending on the distribution of the variable; categorical variables will be displayed as counts with corresponding percentages. Differences between the two treatment groups in terms of continuous variables will be tested by the independent *T*-test or the Wilcoxon rank sum test, depending on the distribution of the variable. Differences in categorical variables will be tested by the Chi-square test or the Fisher exact test.

The non-inferiority between BSCT and TAU in salivary cotinine validated 12 months’ prolonged abstinence rate will be analyzed by calculating the 95% confidence interval of the observed difference in the abstinence rate and by comparing that to the previously defined non-inferiority margin of 5%.

To assess whether BSCT leads to a decrease in treatment costs compared to TAU, an incremental cost-effectiveness ratio (ICER) will be calculated using treatment costs and abstinence rate.

To assess whether BSCT leads to improved satisfaction among patients and counsellors compared to TAU, satisfaction (based on the middle and long-term evaluation) will be tested between the two groups by applying the independent *T*-test or the Wilcoxon rank sum test.

Both baseline predictors - moderators of intervention effect - and dynamic predictors - mechanisms through which effects occur - will be tested using moderator and mediator analyses [49, 50], including all potential co-variates such as nicotine dependence, cognitive determinants (for example attitude and self-efficacy), medical conditions and mental states (for example depression and anxiety), adherence and internet skills.

Whether the level of adherence to BSCT is related to prolonged abstinence will be tested by the independent *T*-test or the Wilcoxon rank sum test.

All analyses will be performed based on the intention-to-treat principle and will be performed in SPSS version 20.0.

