### Randomization

Patients will be randomly assigned to either BSCT or TAU. Randomization will be performed at the individual level (allocation ratio 1:1) using QMinim Online Minimization (http://qminim.sourceforge.net/) [16]. The minimization will be stratified according to: (1) level of internet skills [17]; (2) level of nicotine dependence [18]); and (3) the quitting strategy favored by the patient (stop at once, gradual change, scheduled reduced smoking; for details see below the description of the study intervention). The data used for the QMinim minimization will be collected using the baseline questionnaire, which will be filled in online by the patient at home.

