### Sample size

For this RCT 344 patients will be needed. This is based on the following assumptions and calculations.

Since we expect that BSCT will be at least non-inferior to TAU concerning prolonged abstinence, we conduct a non-inferiority trial. Furthermore, we expect BSCT to be better at secondary factors such as costs, adherence and satisfaction [46].

Based on previous studies involving smoking cessation treatment within the organization involved in this RCT [4, 5] and meta analyses [3], a cotinine-validated prolonged 12 months’ abstinence rate of 10% (based on intention-to-treat analysis) with TAU is expected. Based on the expected benefits of BSCT the estimated abstinence rate for BSCT is 15%. If BSCT leads to an abstinence rate of not lower than 5% it will be regarded as non-inferior. With a power of 80% and α of 0,025 172 patients per group are needed for this RCT (calculated with PASS).

The 5% criterion is based on the three assumptions described below:A validated prolonged abstinence rate of 5% may still be considered as superior to (1) a non-intervention condition which is estimated at a 1.4% abstinence rate and to (2) a 2.6% abstinence in a minimal intervention condition in clinical populations such as COPD patients [47].In a worst-case scenario, BSCT patients will fail to use the web-based part of the intervention completely, and adhere to the face-to-face component only. This would reduce their exposure to the intervention by 50% compared to full adherence to TAU. Assuming a linear dose–response relationship of intervention intensity and likelihood of abstinence the 10% abstinence rate estimated for TAU would then be reduced by 50% to a 5% abstinence rate.Although a 5% abstinence rate is considerably lower than the estimated 10% in TAU, the secondary benefits of BSCT - such as client satisfaction - need to be taken into account. Thus, even at a lower effectiveness we expect that BSCT can still be the preferred treatment.

Based on the experience that approximately 360 patients per year start a cessation treatment at SRP, it is expected that recruitment, treatment and follow-measurements of the 344 patients needed for this RCT will take 3 to 4 years.

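### Allocation is minimised on three baseline factors but the primary non-inferiority interval is unadjusted: a cheap, small gain in efficiency, with no threat to validity or to the stated power

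*Protocol article*

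**What the plan says.** **Design.** Under Randomization, the protocol article states: "Randomization will be performed at the individual level (allocation ratio 1:1) using QMinim Online Minimization". It then introduces the balancing factors with "The minimization will be stratified according to" and lists internet skills, nicotine dependence and the quitting strategy that the patient favours. All three come from the baseline questionnaire.

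**Analysis.** Under Data analysis/Statistical methods, non-inferiority is assessed by "calculating the 95% confidence interval of the observed difference in the abstinence rate" and setting it against a margin of 5%. No covariate is named for this analysis. Covariates, including nicotine dependence and internet skills, appear only in the later moderator and mediator analyses.

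**Sample size.** The expected control rate is given as "a cotinine-validated prolonged 12 months’ abstinence rate of 10% (based on intention-to-treat analysis) with TAU is expected", the blended arm is put at 15%, and the criterion reads "If BSCT leads to an abstinence rate of not lower than 5% it will be regarded as non-inferior". The result is "With a power of 80% and α of 0,025 172 patients per group are needed". No allowance for covariate adjustment appears.

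**The concern.** When allocation is balanced on factors that predict the outcome, the difference between arms varies less from trial to trial than under simple randomisation. The ordinary standard error of a difference in proportions does not reflect this. The crude interval is then somewhat wider than it needs to be, and in a non-inferiority trial a wider interval makes a conclusion less likely.

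The article itself treats the factors as possibly predictive. It classes internet skills among baseline predictors and moderators (Table 2). It notes that gradual quitting may do less well than abrupt quitting (Study intervention). It relies on balance in quitting strategy to protect internal validity (Discussion). At stake is some precision that could be had from data already in hand, and the usual principle that the analysis should reflect how patients were allocated.

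**Working it through.** **1. Inputs.** From Sample size: TAU 10%, BSCT 15%, 172 per arm, power 80%, α 0.025. I read α as one-sided, which matches a two-sided 95% interval. The margin is 5 percentage points (10% less the 5% floor). The share of outcome variance explained by the three factors, R², is not in the article. I assume a range from 0% to about 10%.

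**2. Reproducing the stated size.** With unpooled variance,

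n = (1.960 + 0.842)² × (0.10×0.90 + 0.15×0.85) / (0.05 + 0.05)² = 7.849 × 0.2175 / 0.01 = 170.7, so 171 per arm.

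A pooled-variance version gives 171.4, so 172. The stated figure thus rests on a crude risk difference. At 172 per arm the standard error is √(0.2175/172) = 0.03556, and power is Φ(0.10/0.03556 − 1.96) = Φ(0.852) = 80.3%.

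**3. What adjustment adds at 15% v 10%.** Large-sample approximation: the adjusted standard error is the crude one times √(1 − R²).

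| R² | Adjusted power | Half-width (points) | One-sided error of crude interval |
|---|---|---|---|
| 0% | 80.3% | 6.97 | 0.0250 |
| 2% | 81.1% | 6.90 | 0.0239 |
| 5% | 82.3% | 6.79 | 0.0222 |
| 10% | 84.2% | 6.61 | 0.0194 |

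The last column is 1 − Φ(1.96/√(1 − R²)). It assumes perfect balance and shows the conservatism of the crude interval.

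The 80.3% is not quite the right comparator when R² is above zero, because balance alone already helps the crude analysis. At R² = 10% crude power is Φ(0.852/0.9487) = 81.5%, so adjustment adds 84.2 − 81.5 = 2.7 points.

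**4. Check by simulation.** 344 patients; biased-coin minimisation (probability 0.8) on factors with 2, 3 and 3 equally frequent levels; the same odds ratio per step for each factor; crude Wald interval v linear-model risk difference with robust standard error; 3,000 runs per scenario (Monte Carlo error about 0.7 points).

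| Odds ratio per step (R²) | Crude power | Adjusted power |
|---|---|---|
| 1 (0%) | 79.2% | 78.9% |
| 1.5 (about 2–3%) | 80.9% | 81.5% |
| 1.8 (about 5–7%) | 81.5% | 82.8% |
| 2.5 (about 11–14%) | 82.5% | 85.3% |

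The gain runs from nil to about 3 points. With BSCT truly at 5%, simulated one-sided error was 2.2% to 3.5% for crude and 2.6% to 3.6% for adjusted. Within a scenario the two differed by at most 0.4 points. The excess over 2.5% comes from the Wald approximation at low rates and affects both methods.

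**5. Both arms at 10%.** The standard error is √(2 × 0.09/172) = 0.03235, the half-width 1.96 × 0.03235 = 6.34 points, and power Φ(0.05/0.03235 − 1.96) = Φ(−0.414) = 33.9%. Two illustrative gradients over equal-sized strata give R²:

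- 5/10/15%: (25 + 0 + 25)/3 × 10⁻⁴ / 0.09 = 1.9%
- 2/5/11/22%: (64 + 25 + 1 + 144)/4 × 10⁻⁴ / 0.09 = 6.5%

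| R² | Adjusted power | Half-width (points) |
|---|---|---|
| 1.9% | 34.5% | 6.28 |
| 6.5% | 35.9% | 6.13 |
| 10% | 37.0% | 6.01 |

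Against 33.9% the gain is 0 to 2 points up to R² = 6.5%, and about 3 at 10%. Here balance lowers crude power slightly, to Φ(−0.414/√0.935) = 33.4% at 6.5% and Φ(−0.414/0.9487) = 33.1% at 10%. That adds between half a point and a point to the gain and does not change the picture. To bring the half-width down to 5 points, R² would have to be 1 − (5/6.34)² = 38%.

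**The case against.** The strongest reply is that covariate sets and interval methods belong in a statistical analysis plan, which is not shown, and that the article nowhere rules out an adjusted estimate. This stands in part. A separate plan may already adjust. But the article does not leave the method open: it names the observed difference as the quantity for the primary interval.

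A second reply is that planned analysis and sample size agree with each other, and that the crude interval errs, if at all, on the safe side. This stands in full.

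A third is that no effect of any of the three factors is quantified in the article. This also stands. If they predict nothing, the gain is nil, and the 2/5/11/22% gradient used above is an elevenfold contrast without a source in the article.

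A reader might go further and infer that the trial is throwing away precision it has already paid for, or is underpowered because of the crude analysis. The article does not support that. The 344 patients were sized without any such gain, and the Discussion defends balance on quitting strategy by internal validity, not by precision.

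**Conclusion.** The mismatch between design and primary analysis is real and is stated in the article. Its consequence is small: a slightly conservative interval if the factors are prognostic, costing nil to about 3 points of power at 15% v 10%. With equal arms at 10% it costs about 0 to 2 points for up to 6.5% of variance explained, and about 3 at 10%. These sizes rest on an assumed R² of 0% to about 10% and, in the simulation, on assumed factor levels and effects.

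Confidence is high that the analysis does not follow the allocation, and low on how much is lost. Validity and the stated 80% power are not in question. It would also be wrong to infer that adjustment rescues the trial if the arms are merely equal. Power would stay in the mid-thirties and the half-width above 6 points, because that weakness comes from the sample size and the assumed 5-point benefit of BSCT. Severity is low: a free or cheap improvement.

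**What to change.** Before outcome data are examined, pre-specify as the primary estimate the risk difference adjusted for the three minimisation factors. Obtain it by standardisation from a logistic model, with a delta-method or bootstrap 95% interval, and compare its lower limit with the same 5-point margin. Report the crude difference as a sensitivity analysis.

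Keep the model small, because only about 172 × 0.10 + 172 × 0.15 = 17 + 26 = 43 events are expected. Enter nicotine dependence and internet skills as scores, and merge sparse quitting-strategy levels by a rule set in advance. A Mantel-Haenszel estimate over the cross-classified factors is not advisable. Five dependence levels, three strategies and an assumed two internet-skill levels make 30 strata, or about 1.4 events each.

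The cost is a paragraph of analysis-plan wording, a little more programming and a small dependence on the model with few events. No further data or patients are needed, since the factors are collected before allocation. Fixing one adjusted model in advance also removes any later choice between crude and adjusted results in this open-label trial.

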### Measurements

The time-points of the follow-up measurements are tied to the estimated stop-date, which is appropriate for aid-to-cessation trials [26]. The expected stop-date is 3 months after treatment start, which is later than in common cessation treatments where quitting usually is expected within 1 to 3 weeks. In total there will be four follow-up measurements with measurement 3 and 4 (9 and 15 months follow-up) to be conducted at standard time points (i.e. 6 and 12 months after the expected stop-date):3 months after treatment start, expected stop-date, (3 months follow-up);6 months after treatment start, end of treatment and 3 months after expected stop-date, (6 months follow-up);9 months after treatment start, 3 months after end of treatment, 6 months after expected stop-date, (9 months follow-up); and15 months after treatment start, 9 months after end of treatment, 12 months after expected stop-date, (15 months follow-up).

A measurement schedule can be found in Table 2. The biochemical measurements will be done when the patient is at the hospital for a face-to-face session in week 1 (Exhaled CO; baseline/month 0), week 14 (Exhaled CO & Cotinine level; month 3) and week 22 (Exhaled CO; month 5). For the final biochemical measurement (Exhaled CO & Cotinine Level; month 15) which will take place 12 month after the expected stop date in month 3, the patient will have to return to the hospital. All other assessments will be done using online questionnaires which the patients will complete at home.

**Table 2 Tab2:** Measurement schedule

Variables	Measurement at month					
	0	3	5	6	9	15
Primary outcome						
Cotinine level		X				X
Secondary outcomes						
Nicotine dependence (Fagerström)	X			X	X	
MAP-HSS + smoking related complaints of smokers	X			X	X	X
Depression, anxiety and stress (DASS21)	X			X	X	X
Quality of Life (Euroqol 5D)	X			X		
Smoking status	X	X		X	X	X
Adherence						X
Costs						X
Baseline predictors and moderators of treatment effect						
Internet Skills	X					
Readiness to change	X					
Attitude	X			X	X	
Social Influence	X					
Self-Efficacy	X			X		
Alcohol/substance (mis)use	X			X		
Descriptive variables						
Patient characteristics and medical history	X					
Smoking history	X					
Stop Smoking History	X					
Other information of interest						
Evaluation of treatment		X		X	X	X
Exhaled carbon monoxide (CO) level	X	X	X			X

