## Instruments

### Primary outcome (Cotinine level)

The primary outcome parameter will be biochemically validated prolonged abstinence [26] at 15 months from the start of the smoking cessation treatment. Saliva cotinine level will be measured as biochemical verification of abstinence only by those patients that report quitting smoking in the previous online questionnaires [27]. Prolonged abstinence is defined as having salivary cotinine levels < 20 ng/ml [28] that validate both the self- reported abstinence after the self-chosen stop date – usually 3 months after start - and the self-reported abstinence at 15 month follow-up. Patients not reporting abstinence or with a higher cotinine level on any of these follow-ups will be regarded as smokers as well as patients who are lost to follow-up. A 0,5–1 ml salivary sample will be collected for cotinine assessment by means of a Salivette (Sarstedt AG & Co., Nümbrecht, Germany). Under supervision, patients will have to chew on a cotton swab for 1min to stimulate the saliva flow rate. All saliva specimens will be frozen until assayed and transported to the laboratory for the determination of the cotinine level using a gas chromatography technique.

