### Attitude, social influence and self-efficacy

According to the ASE Model [37, 38] the intention to stop smoking is determined by three motivational factors: Attitude, Social Influence and Self-Efficacy. Attitude [39, 40] refers to the overall evaluation of smoking cessation. Attitude will be measured with an indirect, belief-based scale for perceived pros (four items: improved health for the patient, improved health for the patient’s personal environment, lower risk of lung cancer, improved self-satisfaction) and cons (four items: suffering withdrawal symptoms, missing smoking, less ability to relax, feeling bored). Social influence refers to three distinctive constructs: social norms, perceived behaviour of others and direct support. It will be measured recording if the patient is stimulated to stop smoking by acquaintances, if his/her partners is a smoker and how many of his/her acquaintances are smokers. Self-Efficacy [41] refers to the confidence in the ability to refrain from smoking in specific high-risk situations, i.e. the situations in which the quitter is tempted to relapse. It will be measured recording six typical relapse situations (e.g. stress or party). The three constructs of the ASE model will be measured using standardized questions developed by the former Dutch foundation STIVORO [34, 42].

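### Attitude, self-efficacy, nicotine dependence and DASS-21 are first repeated at month 6, after the first abstinence check, so a full-sample mediator analysis on these scales cannot tell a mechanism of initial quitting from its consequence

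*Protocol article*

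**What the plan says.** All places are in the protocol article.

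- **Analysis.** Data analysis/Statistical methods announces that "dynamic predictors - mechanisms through which effects occur - will be tested using moderator and mediator analyses". The covariates named are nicotine dependence, cognitive determinants such as attitude and self-efficacy, and "medical conditions and mental states (for example depression and anxiety), adherence and internet skills". All analyses are to follow intention to treat. No rule orders mediator and outcome in time. The Background makes mediators of treatment outcome part of the fourth secondary objective, and the Abstract aims to identify mechanisms of successful cessation.
- **Schedule.** Measurements states: "The expected stop-date is 3 months after treatment start". Table 2 places the Fagerström test at months 0, 6 and 9, DASS-21 at 0, 6, 9 and 15, attitude at 0, 6 and 9, and self-efficacy at 0 and 6. The last two are listed under "Baseline predictors and moderators of treatment effect". At month 3 the table has smoking status, treatment evaluation, cotinine and CO, but none of these four scales.
- **Outcome.** Under Primary outcome, abstinence must be validated after the self-chosen stop date, usually month 3, and again at month 15. The failure rule is: "Patients not reporting abstinence or with a higher cotinine level on any of these follow-ups will be regarded as smokers". The only early cotinine sample is in week 14.
- **Adherence.** This comes from real-time log data and the counsellor's record of techniques. Self-reported adherence is part of the treatment evaluation, which starts at month 3.

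**The concern.** A mediator has to be measured before the outcome it is meant to explain. Here a patient who fails the first check is already a final smoker about three months before any of the four scales is repeated. A patient who has quit may have been abstinent for three months when the scale is filled in.

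The instruments make reverse causation likely. Self-efficacy is defined as "the confidence in the ability to refrain from smoking in specific high-risk situations", which three months of success or failure can plausibly change. The attitude items on drawbacks include withdrawal symptoms and missing smoking. The Fagerström test asks about the first cigarette of the day, so its month-6 score depends directly on whether the patient still smokes.

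At stake is part of secondary objective 4: a score that merely follows quitting could be reported as a reason for it. A later analysis plan can choose a better model, but it cannot recover values that were never collected.

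**Working it through.** **1. The plan's own figure.** Inputs from Sample size: 10% in the face-to-face arm (TAU), 15% in BSCT, margin 5 points, one-sided α 0.025, power 80%.
n per arm = (1.960 + 0.842)² × (0.10×0.90 + 0.15×0.85) / (0.15 − 0.10 + 0.05)² = 7.849 × 0.2175 / 0.01 = 170.7, so 171. With pooled variance it is 171.7, so 172 as stated. Power at 172 per arm is 80.3%. No mediator timing enters this calculation.

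**2. How many outcomes are fixed before month 6.** The stated rates imply 17.2 + 25.8 = 43 final abstainers of 344. The month-3 pass rate is not given, so a range is shown.

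| Assumed month-3 pass rate | Already a final smoker | Still open |
|---|---|---|
| 20% | 275 | 69 |
| 30% | 241 | 103 |
| 40% | 206 | 138 |
| 50% | 172 | 172 |

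**3. False score-outcome association, full sample.** Simulated with 344 patients and 4,000 runs per setting. The score has no effect on abstinence, but quitting by month 3 shifts the month-6 score by an assumed amount. Share of runs with p < 0.05 (nominal 5%):

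| Pass rate | 0.3 SD | 0.5 SD | 0.8 SD |
|---|---|---|---|
| 20% | 38% | 79% | 99% |
| 30% | 31% | 66% | 97% |
| 50% | 18% | 41% | 75% |

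The baseline score in the same runs stays at about 5%.

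**4. False indirect effect.** Assumed month-3 quitting is 25% (TAU) and 37.5% (BSCT), with 40% of quitters still abstinent at month 15. This returns the plan's rates: 0.25 × 0.40 = 10% and 0.375 × 0.40 = 15%. The arm-to-score path is linear, the score-to-outcome path is logistic, and the product has a Monte Carlo 95% interval.

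- Score-outcome path significant: 62%, 95% and 99% at 0.5, 0.8 and 1.0 SD.
- Indirect effect declared: 5%, 11% and 21% in one set of 800 runs per shift; a rerun gave about 4% to 17% over the same shifts.
- With equal quitting in both arms: about 2% to 6%.

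**5. Which restriction removes the artefact.** Among month-3 quitters only, the false-positive rate is about 5% if the shift depends only on month-3 status. If 30% of them relapse by month 6 and lose the shift, it is 22–62%. Among patients abstinent at both month 3 and month 6 it is about 5%.

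**The case against.** Four arguments stand on the other side.

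- **Not every mediator is affected.** A reader might infer that all candidates are measured too late. The document does not support that. Adherence is recorded during treatment, although Table 2 marks it at month 15, and is also asked about at month 3. It is an obvious candidate mechanism for a change in delivery mode. Internet skills is measured only at baseline, so it can be a moderator but not a late mediator.
- **The data are not useless.** A reader might infer that mechanism and consequence can never be separated. For patients who pass the first check the outcome is still open at month 6, and smoking status is already collected at months 3, 6, 9 and 15. Maintenance can be studied without new data.
- **The large percentages are not mediation conclusions.** The 62–99% refers to one path. The indirect effect is far less inflated, and with equal arms hardly at all.
- **The model may be left to an analysis plan.** The article does not commit to a full-sample regression on the primary outcome, and the questionnaire schedule reflects a stated wish to limit burden.

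The first three narrow the point and are accepted. The fourth stands only in part. The intention-to-treat statement and the wording of the objective point to the full sample, and Table 2 fixes the gap whatever model is chosen.

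It is also fair to say that the first check is tied to a self-chosen stop date that is only usually at month 3. Week 14 is nevertheless the only early cotinine sample.

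**Conclusion.** The point holds for attitude, self-efficacy, nicotine dependence and DASS-21, and for mediation of initial quitting. For these scales a full-sample analysis of month-6 scores against the primary outcome cannot separate mechanism from consequence.

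The main risk is a spurious score-outcome association being read as a mechanism. The risk of a false formal indirect effect is modest, and material only if BSCT clearly raises early quitting and abstinence shifts the score strongly. These sizes rest on assumed month-3 quit rates, an assumed 40% retention and assumed shifts, none of which the document gives. The ordering problem itself follows from the printed schedule and needs no assumption.

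A reader might also infer that the main conclusion of the trial is at risk. It is not: the sample size and the primary non-inferiority test do not use these scales.

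**What to change.** Amend Data analysis/Statistical methods as follows:

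1. Use month-6 scores, adjusted for month 0, only to explain maintenance to month 15 among patients validated abstinent at month 3 and still self-reporting abstinence at month 6. Requiring month 3 alone is not enough (working, step 5).
2. For initial quitting, limit mechanism claims to adherence recorded before the stop date.
3. Report full-sample associations of month-6 scores with the primary outcome as correlates, not mechanisms.

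This needs no new data, only a change of wording. The price is a smaller subgroup selected after randomisation, so its results are exploratory. Under the assumptions in step 4, month-3 quitters number 172 × 0.25 + 172 × 0.375 = 107.5. If 30% relapse by month 6, about 75 remain, of whom 43 are final abstainers.

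Optional, for patients not yet at that point: add the 8 attitude and 6 self-efficacy items (14 in all) to an online questionnaire before the stop date. This means a minor amendment and a small added burden, and patients already past that point cannot supply the values. Adding the items at month 3 is only a partial remedy. In patients who are abstinent those values already follow quitting, and every patient who fails the month-3 check already has a fixed outcome.
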